**Statistical Analysis Plan (SAP)**  
**for**  
**Early rhythm control therapy in patients**  
**with atrial fibrillation**  
**EAST-AFNET 4**  
**Circulating biomolecule sub-study**

## ***2. Synopsis of study design and procedures***

### ***Study Design***

### **3. Description of Analyses**

#### **Deviations from protocol**

As participation in the circulating biomolecules sub-study is not randomized, but open to all participants independent of their intervention, deviations from the protocol do not apply. Regarding the primary analysis, deviations from the study protocol are collected in a standardized manner.

#### **Analysis Population**

The EAST – AFNET 4 study offered all participants participation in a biosample sub-study. Due to regulatory delays, this offer could not be made to the first 399 patients. The analysis population will consist of all patients randomized in the EAST – AFNET 4 trial in whom biosamples were collected.

For comparison of the effect of the randomized intervention, early rhythm control, we will compare intention to treat populations as a primary analysis.

The analysis population will include those patients from the original study who agreed to also contribute to the circulating biomolecules sub-study. These are 1586 patients of which approximately 50% are women and also around 50% received usual care against about 50% that received early treatment.

We will compare clinical characteristics of the sub-study population with the patients not participating in the sub-study to identify potential differences.

#### **Aim of the study**

The study aims to identify circulating biomolecules associated with the **severity level of heart disease**. Promising candidate circulating biomolecules were identified using a modified Delphi approach. Details have been published, [7], [8], [9]. For this purpose, different multivariate analyses are performed. In addition, different machine learning (ML) models will be used to predict the **dependent variables**:

- **1st co-primary outcome** – which is a composite of the variables:

- cardiovascular death
- stroke / transient ischemic attack
- hospitalization
  - due to worsening of heart failure or
  - due to acute coronary syndrome

is a time-to-event endpoint consisting of:

- a categorical, nominal scaled variable that can take the two expressions true or false  
and
- the time from admission of the participant in the study till observation of the event.

- **2nd co-primary outcome** – 'nights spend in hospital per year'

is a numeric, discrete scaled variable that ranges from 0 to  $n$  number of nights. We will add one night to each value to enable log transformation in addition to using the collected number of nights spent in hospital.

- **Primary safety outcome** – which is a composite of death, stroke, and serious adverse events of rhythm control therapy.

To increase power and to explore the effect on all events, recurrent events will be analyzed in a separate analysis. In addition, circulating biomolecules predictive of components of the primary outcome will be analyzed. We will also determine biomolecule concentrations associated with the primary safety outcome, its components, and biomolecule concentrations associated with major bleeding (captured as SAE). To determine factors that affect the primary outcome, we plan an extended multivariate analysis including clinical parameters associated with the primary outcome (see Kirchhof et al NEJM 2020, supplementary data and Metzner et al Europace 2021) and biomolecule concentrations.

- **Secondary outcomes of interest** – Relevant secondary outcomes were estimated at the two-year follow-up visit. These include cognitive function, estimated by the MoCA score; left ventricular function, estimated as ejection fraction in percent; quality of life estimated by the EQ-5D visual analog scale (0-100) and by the SF-12 questionnaire; and rhythm (categorical: sinus rhythm, atrial fibrillation, other). Models will be built to predict these outcomes. Recurrent AF will be defined in two ways: In all patients, AF at the two-year ECG will be used to define recurrent AF. In patients receiving early rhythm control therapy, an unscheduled visit due to AF will be used to define recurrent AF. At a later stage, the analyses of the telemetric ECGs planned in Maastricht will be used to define recurrent AF in patients randomized to early rhythm control. The latter two definitions create an imbalance between the two randomized groups. For continuous parameters, models will be applied to three values, namely 1. The baseline value, 2. The value at two years, and 3. The change between baseline and two years.

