### **Inference Analytics**

It is expected that clinical parameters and biomolecule concentrations will interact in complex ways. These multiple interactions are not well captured by classical regression analyses. On the other hand, multiple regression remains the 'gold standard' in the field. To reflect these complexities and demands, we will train four types of models separately for the 1st primary outcome, the 2nd primary outcome, and the primary safety outcome. Those model types include statistical learning (SL), machine learning, and deep learning (DL) approaches. Furthermore, each of the  $3 * 4 = 12$  models will be trained with clinical confounders and with clinical confounders combined with circulating biomolecules. This gives us the ability to eventually compare 24 models and their reflection of interactions between the clinical parameters and biomolecule concentrations.

- A time-to-event machine learning problem to be solved by different candidate models to be compared against each other. These are namely:
- For 1st primary outcome, 1st primary safety outcome and their components
  - Cox regression – SL - classic approach
  - random survival forest – ML – Tree-based ensemble (bagging)
  - gradient boosted model – ML – Tree-based ensemble (boosting)
  - artificial neural network – DL – multi layer perceptron
- A regression ML-problem to be solved by the following candidate models:
- For 2nd co-primary outcome
  - multiple linear regression – SL - classic approach
  - random forest – ML – Tree-based ensemble (bagging)
  - gradient boosted model – ML – Tree-based ensemble (boosting)
  - artificial neural network – DL – multi layer perceptron

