### Numerical variables

Numerical variables will be **normalized** before being fed into the models for training and testing. Also log-transformation of numeric variables will be applied. As these transformations are crucial for the success of Algorithms that rely on stochastic gradient decent like artificial neural networks, they are not necessary preprocessing steps for tree-based models.

We are going to apply these transformations anyway to compare their impact on the prediction power.

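### Nights in hospital per year has no count model, offset or follow-up weight, and the log(nights + 1) coefficient depends on a constant whose place is not stated

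*SAP*

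**What the plan says.** SAP, Aim of the study, names "nights spend in hospital per year" as the second co-primary outcome. It says the outcome "is a numeric, discrete scaled variable that ranges from 0 to" n nights, and then: "We will add one night to each value to enable log transformation", alongside an analysis of the nights as collected. So two versions are planned, one logged after a shift and one untransformed.

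SAP, Inference Analytics, treats the outcome as "A regression ML-problem to be solved by the following candidate models". The list is "multiple linear regression – SL - classic approach", then a random forest, a gradient boosted model and a neural network. The same section calls multiple regression the field's reference standard.

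SAP, Numerical variables, adds "Also log-transformation of numeric variables will be applied", so that the effect of transformation on prediction can be compared.

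Nowhere does the SAP name a Poisson, negative binomial or hurdle model, an offset, an exposure term or a follow-up weight. It gives no mean, share of zeros, dispersion or follow-up length for this outcome.

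**The concern.** Nights per year is a count divided by time at risk. It has zeros, is likely to be strongly skewed, and is not discrete once divided, although the SAP calls it so. Three things follow.

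- **The constant is arbitrary and its place is not fixed.** The logged analysis changes with the unit to which the one night is added, and the SAP allows more than one reading.
- **The coefficient is hard to use.** Readers will tend to read an exponentiated coefficient from a logged outcome as a rate ratio. With the shift it is not one, and it lies closer to 1.
- **Unequal follow-up is only partly handled.** Dividing by time puts patients on one scale, but unweighted least squares gives a rate from a few months the same weight as a rate from several years. If the collected number of nights means the raw total, that version does not account for follow-up at all.

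At stake is how well the only interpretable model for a co-primary outcome describes the association of each biomolecule with hospital nights.

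**Working it through.** The SAP gives no figure to reproduce for this outcome. Every distributional input below is an assumption; only the sample size comes from the SAP (1,586 patients in Analysis Population; 80% of the 1,585 in Handling errors and missing data is 1,268).

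**1. Where the one night is added.** Take patients followed for 0.5 and 5 years.

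| Nights | Annualise, then add 1 | Add 1 to the total, then annualise | Add 1 to the total, no annualising |
|---|---|---|---|
| 1 in 0.5 years | 1/0.5 + 1 = 3 | 2/0.5 = 4 | 2 |
| 1 in 5 years | 1/5 + 1 = 1.2 | 2/5 = 0.4 | 2 |
| 0 in 0.5 years | 1 | 1/0.5 = 2 | 1 |
| 0 in 5 years | 1 | 1/5 = 0.2 | 1 |

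The three readings give different outcomes. In the second, patients with no nights differ only because their follow-up differs.

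**2. Why the coefficient shrinks.** The derivative of log(x + 1) with respect to log(x) is x/(x + 1). A proportional change therefore passes through in full only when x is large: 0.2/1.2 = 0.17 at 0.2 nights/year, 1/2 = 0.50 at 1, 5/6 = 0.83 at 5, and nothing at zero.

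**3. By how much.** Simulated negative binomial counts, variance mu + k·mu², k from 1 to 8, follow-up fixed at 5 years or uniform over 2 to 8 years, true rate ratio 1.25, 1.5 or 2. Share of the log rate ratio retained on the log(nights per year + 1) scale:

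| Mean nights/year | Share retained |
|---|---|
| 0.5 | 0.16 to 0.34 |
| 1 | 0.20 to 0.47 |
| 2 | 0.25 to 0.60 |
| 5 | 0.34 to 0.76 |
| 10 | 0.38 to 0.85 |
| 20 | 0.44 to 0.90 |

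The loss is thus 1 − 0.90 = 10% to 1 − 0.16 = 84%. A true rate ratio of 1.5 appears as 1.07 to 1.44. With the one night added to the raw total, 0.28 to 0.98 is retained. Fixed and variable follow-up gave almost the same shrinkage, so it comes from the shift, the zeros and the dispersion.

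**4. Power, binary predictor.** n = 1,586, true rate ratio 1.25, 150 runs per row:

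| Mean, k | Linear on log(rate + 1): exp(beta), power | Negative binomial with offset: rate ratio, power |
|---|---|---|
| 1, 2 | 1.08, 0.74 | 1.25, 0.85 |
| 5, 2 | 1.15, 0.79 | 1.25, 0.88 |
| 5, 4 | 1.11, 0.45 | 1.25, 0.62 |
| 10, 4 | 1.12, 0.37 | 1.23, 0.54 |

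**5. Power, per SD of a continuous predictor, raw scale included.** n = 1,268, mean 5, 10% followed for under 2 years, true rate ratio 1.15, two sets of 150 runs:

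- k = 3: log version 1.08 with 69% and 72% power; raw 83% and 82%; negative binomial 1.15 and 1.16 with 82% and 83%.
- k = 1.5: log version 1.09 and 1.10 with 91% and 92%; raw 97% and about 100%; negative binomial 1.15 with 97% and about 100%.

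A further check at means of 1 and 5 also generated nights as multi-night stays. exp(beta) was 1.04 to 1.10 for the log version against 1.14 to 1.16 for negative binomial. Power was 0.43 to 0.93 (log), 0.44 to 0.95 (raw) and 0.47 to 0.96 (negative binomial).

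**6. How unequal the precision is.** Under this variance, an annualised rate with mean λ over t years has variance λ/t + kλ². For λ = 5, k = 3: 10 + 75 = 85 at 0.5 years and 1 + 75 = 76 at 5 years, a ratio of 1.12. For λ = 1, k = 2: 2 + 2 = 4 and 0.2 + 2 = 2.2, a ratio of 1.82. Only the first term shrinks with follow-up, which helps explain why raw-scale regression holds up.

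**The case against.** The strongest reply is that the SAP promises no rate ratio. Its aim for this outcome is prediction; linear regression is one of four candidates, and permutation importance identifies the biomolecules. A log(x + 1) coefficient is then a different quantity, not a biased one. That stands, which is why the shrinkage is stated only for the coefficient read as a log rate ratio. It does not remove the dependence on an unplaced constant, and the linear model remains the only one of the four with a directly interpretable effect.

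Second, most of the simulations generate negative binomial data and so favour that model. This also stands. The check with multi-night stays points the same way but with modest power differences. The shrinkage itself does not depend on that choice; step 2 shows it comes from the shift.

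Four stronger readings are tempting and are not supported:

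- A reader might infer that the plan ignores follow-up length. The outcome is defined per year, so length enters the value. This reading would hold only for the untransformed version, and only if it is a raw total.
- A reader might infer that the log version halves the rate ratio. It shrinks the log rate ratio, and by about half only in part of the assumed range (at 5 nights/year and k = 4, 0.47 to 0.50 is retained).
- A reader might infer that all planned linear analyses lose precision. Raw-scale regression had power close to negative binomial.
- A reader might infer that early deaths and drop-outs with extreme rates dominate the fit. Nothing here shows that.

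**Conclusion.** The point holds as a cheap improvement in method. The classical analysis of a co-primary count outcome uses linear models without an offset or weight, and the placing of the added night is undefined. The main gain from a change is an interpretable rate ratio without the shrinkage, and follow-up handled in the model. A modest power gain applies in most settings over the log version and hardly at all over the raw version.

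The 10% to 84% shrinkage rests on assumed means of 0.5 to 20 nights/year, k of 1 to 8 and the one night added after annualising. The SAP's silence on these inputs rules out a single figure. Type I error is not the complaint: with no effect, rejection was 0.00 to 0.07 (log version) and 0.02 to 0.09 (negative binomial) in step 4's settings, too few runs to rank the models.

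**What to change.** - In Inference Analytics, make the classical model for this outcome a negative binomial regression of total nights, with log follow-up time as offset and robust standard errors, reporting rate ratios per SD of each biomolecule.
- Keep linear regression on the raw and log(nights + 1) values as sensitivity analyses.
- In Aim of the study, state whether each version is annualised and whether the one night is added before or after annualising, and drop the description of an annualised value as discrete.
- Weight the forest, boosting and network models by follow-up time. A count loss with exposure is an alternative; step 6 shows that weights strictly proportional to time can overstate the precision gain when dispersion between patients is large.

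Cost: a few sentences in the SAP and slightly more analysis work. The regression is a standard procedure in R, which the SAP already lists. No new data are needed beyond each patient's total nights and follow-up time.

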## EAST-AFNET circulating biomolecules sub-study

- **Specific hypotheses.** Based on our biomedical knowledge, we developed specific hypotheses that will be tested in the EAST – AFNET 4 biomarker sub-study. These include the following:
  1. BMP10 concentrations are associated with recurrent AF and affect recurrent AF differentially depending on the use of sodium channel blockers (flecainide, propafenone).
  2. FGF23 concentrations are associated with recurrent AF.
  3. A combination of ANG2, FGF23, and BMP10 predicts recurrent AF better than natriuretic peptides.
  4. ESM1 concentrations are associated with stroke (both prior stroke at baseline and future stroke during FU) and with the composite of stroke and cardiovascular death
  5. The ABC bleeding score is associated with major bleeding
  6. The ABC stroke score is associated with stroke and with the composite of stroke and cardiovascular death
  7. BNP is associated with heart failure hospitalizations and with the composite of death or heart failure hospitalization
  8. Angiotensin 2, FGF23 (alone or in combination or in combination with ESM1) are strong predictors for stroke or stroke and ACS, or stroke + ACS + CV death

- The 14 circulating biomolecules:
  - ANG2
  - BMP10
  - Cancer-Antigen 125 (CA-125)
  - Cardiac C-Reactive Protein High Sensitive
  - Creatinine (enzymatic determination)
  - D-Dimer [Explicit units would be "ug FEU/mL]
  - ESM1
  - FBP3
  - FGF23
  - Growth Differentiation Factor-15
  - Interleukin-6
  - IGFBP7
  - NT-proBNP
  - Troponin T high sensitive (cTnT-hs)

all numeric, continuous scaled

To enable evaluation of these circulating biomolecules in context with clinical information, a list of parameters that are associated with the primary outcome will be included in the analysis. A preliminary list will be taken from the existing analyses in the trial. If there are too many candidates, we will do some variable reduction to discard “redundant” variables without using the association with the endpoints to inform that decision (e. g. correlations, PCA, etc.).

See supplement to the main results publication for a list of preselected parameters.

- additional **clinical** parameters collected at baseline:
  - age
    - numeric, discrete scaled
  - gender
    - categorical, nominal scaled – dichotomous
  - random group
    - categorical, nominal scaled – dichotomous
- BMI
  - numeric, continuous scaled
- Heart Failure, determined using heart failure symptoms and LVEF

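### Covariates are chosen for association with a composite that contains no bleeding, and the printed list names no anticoagulant, so D-dimer's associations with bleeding, and possibly stroke, may be biased

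*SAP*

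**What the plan says.** **Outcomes.** In Aim of the study, the first co-primary outcome combines cardiovascular death, stroke or TIA, and hospitalisation for worsening heart failure or acute coronary syndrome. Beyond the composite, "circulating biomolecules predictive of components of the primary outcome will be analyzed", which brings in stroke on its own. The same section adds the safety outcome with its components, and "biomolecule concentrations associated with major bleeding (captured as SAE").

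**Markers.** The section EAST-AFNET circulating biomolecules sub-study lists 14 biomolecules. D-dimer is one of them.

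**Covariates.** The same section states the rule: "a list of parameters that are associated with the primary outcome will be included in the analysis". A preliminary list comes from existing trial analyses and may be thinned for redundancy without looking at the endpoints. The reader is then told: "See supplement to the main results publication for a list of preselected parameters". The items printed as clinical "parameters collected at baseline" cover demography, randomised group, comorbidity, symptoms, AF pattern, blood pressure, left atrial size, kidney function and questionnaire scores. No drug treatment is among them, and the SAP never mentions anticoagulation. The only drugs it names are in hypothesis 1, where the effect of BMP10 may differ "depending on the use of sodium channel blockers (flecainide, propafenone").

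**Use in models.** Inference Analytics treats these clinical variables as confounders and fits each model with them alone and with them plus the biomolecules.

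**The concern.** A confounder has to be judged against the outcome being modelled. A rule tied to a composite without bleeding gives no assurance that determinants of bleeding enter the bleeding analysis, and the SAP states no other rule for it.

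Anticoagulation is the obvious candidate in an atrial fibrillation population. If it lowers D-dimer, lowers stroke risk and raises bleeding risk, it is a common cause of the marker level and of both outcomes. Low D-dimer then partly marks treated patients. A D-dimer with no effect of its own would look harmful for stroke and slightly protective for bleeding, and one that truly predicts bleeding would be attenuated. Separately, a clinical-only model without anticoagulation would be an incomplete comparator for judging what the biomolecules add for stroke and bleeding.

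**Working it through.** The SAP gives no figure for this point, so there is nothing to reproduce. The check asks how large the bias could be if anticoagulation is left out.

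**Inputs, all assumed (none is in the SAP):**
- share anticoagulated at sampling, p: 0.80, 0.90 or 0.95
- log D-dimer lower on treatment by s = 0.5 to 1.0 SD
- hazard ratio of anticoagulation, h: 0.4 for stroke, 2 for bleeding
- D-dimer has no effect of its own, events are rare, treatment is unrelated to other risk factors, and there are no other covariates

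**Formula.** Let log D-dimer be normal with SD 1, mean 0 untreated and −s treated.
- Treated share among events: w = p·h / (p·h + 1 − p).
- Mean marker in events: −w·s; in all patients: −p·s.
- The Cox slope b per within-group SD solves b − s·t(b) = −w·s, with t(b) = p·exp(−b·s) / (p·exp(−b·s) + 1 − p).
- Apparent hazard ratio per overall SD: exp(b·√(1 + p(1 − p)s²)).

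**Worked case: stroke, p = 0.9, s = 1, h = 0.4.**
- w = 0.36 / 0.46 = 0.783, so the mean marker is −0.783 in events against −0.900 overall.
- b = 0.107. Check: t = 0.808 / 0.908 = 0.890, and 0.107 − 0.890 = −0.783.
- Overall SD = √1.09 = 1.044. Hazard ratio = exp(0.107 × 1.044) = 1.12.

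**All settings (s = 0.5 to s = 1.0), marker truly null:**

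| Treated | Stroke HR per SD | Bleeding HR per SD |
|---|---|---|
| 80% | 1.10 to 1.19 | 0.96 to 0.92 |
| 90% | 1.06 to 1.12 | 0.98 to 0.96 |
| 95% | 1.03 to 1.07 | 0.99 to 0.98 |
| 100% | 1.00 | 1.00 |

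**Effect on a 5% two-sided test**, from P(|Z + log(HR)·√events| > 1.96) with 50 events assumed for each outcome:
- Stroke: 10–23% at 80% treated, 7–12% at 90%, 5.6–7.4% at 95%.
- Bleeding: 6.1–9.0%, 5.3–6.2% and 5.1–5.3%.

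**Second method.** Split D-dimer at the median and use RR = [1 + pH(R − 1)] / [1 + pL(R − 1)], where pH and pL are the treated shares in the high and low halves and R is the effect of treatment on the outcome. At 90% treated and s = 0.5, pH = 0.865 and pL = 0.935. With R = 0.35 for stroke, RR = 0.438 / 0.392 = 1.12. With R = 2 for bleeding, RR = 1.865 / 1.935 = 0.96. Over a wider grid (50–95% treated, s = 0.2 to 1.0, R from 0.35 to 0.8 for stroke and 1.3 to 2.0 for bleeding), stroke RR runs from 1.004 to 1.46 and bleeding RR from 0.77 to 0.996. Under this model, adjusting for anticoagulation returns both to 1.00.

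**The case against.** Several objections carry weight.

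- **The covariate list is not closed.** A reader might infer that anticoagulation is absent from the models. The documents show only that it is absent from the printed items. The SAP points to a supplement, and for the extended multivariate analysis to two trial publications; either could include it.
- **Stroke is in the composite.** If anticoagulation strongly lowers stroke risk, the stated rule could select it, although the other components dilute the signal. The criticism of the rule is therefore firm for bleeding and conditional for stroke.
- **Every size is assumed.** A reader might infer that D-dimer's link with stroke is inflated and its link with bleeding masked. That cannot be stated as fact. At 90–95% treated, a null marker shows a bleeding hazard ratio of 0.96–0.99, and at 95% the false-positive rates are near nominal.
- **Prescribing follows risk.** If higher-risk patients are treated more often, the stroke bias could be offset. The calculation ignores this and leaves out the printed covariates related to prescribing.
- **Reach.** A reader might carry the D-dimer argument over to hypotheses 4, 5, 6 and 8. They concern ESM1, the ABC scores, ANG2 and FGF23. The documents give no route by which anticoagulation changes these, and sharing an outcome is not confounding.
- **Prediction.** Much of the aim is prediction, where confounding is not itself an error. Yet the SAP calls its clinical variables confounders and goes on to identify biomolecules as risk factors.

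What survives is that the one stated selection rule does not suit the bleeding analysis, and that nothing in the SAP secures anticoagulation in the stroke or bleeding models. The SAP does not say which covariates the bleeding analysis will use.

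**Conclusion.** The point holds in conditional form. Selecting covariates by association with a composite that excludes bleeding is a poor rule for an analysis of bleeding, and the visible list contains no anticoagulant. D-dimer's association with bleeding may be biased toward or below the null. Its association with stroke may be biased upward if the unseen list also omits anticoagulation.

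The bias could matter for stroke at around 80% treated, is modest at 90%, and fades as the treated share approaches 100%. For bleeding it is smaller throughout. This rests on assumed drug effects, an unknown treated share, and prescribing unrelated to risk. For the other markers and for hypotheses 4, 5, 6 and 8, the point is only that the clinical comparator may be incomplete.

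**What to change.** Amend the SAP as follows:

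1. Choose covariates for the major bleeding analysis by their relevance to bleeding, and list them.
2. Prespecify baseline oral anticoagulation as recorded at blood sampling (none / vitamin K antagonist / direct oral anticoagulant) in both the clinical-only and the clinical-plus-biomolecule models for stroke, the safety outcome and major bleeding. Exempt it from the redundancy-based variable reduction.
3. Report its distribution. If nearly all patients are treated, this alone shows that the bias is small.
4. Give the D-dimer estimate within anticoagulated patients as a sensitivity analysis.

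If the supplement list already contains anticoagulation, print it in the SAP and confirm that it enters the stroke and bleeding models.

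The cost is wording and about two more degrees of freedom (three categories) in models of rare events. Hypothesis 1 already requires data on drug use; that baseline anticoagulation was recorded as well is an inference to confirm.
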